#### Participants considered for trial

This will be a prospective longitudinal study involving all patients successively scheduled for operation for symptomatic prolapse POP–Q grade II or III and coexisting SUI, who will be included in the study after informed consent has been obtained. Patients will be recruited in the Department of Obstetrics and Gynaecology at the University of Szeged. The study will be conducted for an estimated maximum of 18 months (between August 2016 and December 2017). Table 1 provides an overview of the patient recruitment and evaluation plan.

**Table 1 Tab1:** Schedule of assessments/data collection

Assessment	Recruitment before intervention phase	Intervention (surgery)	Follow-up				
			6 weeks	6 months	1 years	2 years	3 years
Assessment of eligibility criteria	x						
Written informed consent	x						
Gynecological examination: incontinence symptoms	x	x	x	x	x	x	x
Gynecological examination: prolapse	x	x	x	x	x	x	x
Urodynamic examination	x				x		x
Adverse events		x	x	x	x	x	x
Questionnaires: PISQ-12 and PFDI	x		x	x	x	x	x
Introital sonography	x				x		x
Urine culture	x			x	x	x	x

The symptomatic POP–Q Stage II–III (determined by the gynecological examination using the International Continence Society quantification system) [18] anterior vaginal wall prolapse is defined as the maximum extent of the prolapsed anterior and middle compartments being within 1 cm above and 6 cm below the hymen [19, 20]. According to the international POP guidelines (the EBU and NICE guidelines) [21, 22], if the condition disrupts the patient’s life and non-surgical treatment options have not helped, it should be treated surgically.

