## Statistical methods

### Hypothesis

Alternative hypothesis for primary outcome: it is hypothesized that the group undergoing the modified transvaginal mesh operation will have a statistically higher improvement of continence measured by gynecological and urodynamic examination, and from the questionnaire administered before and after the intervention phase.

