### Statistical analyses

Analysis of the patients will follow the CONSORT flow diagram (Fig. 1) through the phases of the study (enrollment [assessed, excluded, randomized], allocation [control group and experimental group with intervention received or not received], follow-up [lost to follow-up, discontinued intervention] and analysis) [30].

All statistical analyses will be conducted using SPSS software version 22 (IBM, Armonk, NY, USA). All tests will be two-sided and significance will be set at *P* < 0.05. Efficacy measurements were adjusted by intention-to-treat analysis. Missing values will be replaced using the last observation carried forward (LOCF) method. No subgroup analyses are planned. Standard deviations, 95% confidence intervals, and median will be used for the descriptive analyses. Primary and secondary outcome analysis: the Chi-square test or Fisher’s exact test will be employed to identify any objective outcome differences among groups.

Generally, continuous data will be checked for normality using the Shapiro–Wilk test. If the normality assumption is violated, then PISQ-12 and PFDI scores as tertiary outcomes will be normalized by log transformation (log10(x)). Univariate-repeated measure analysis of variance (ANOVA) will be used to determine the secondary outcome between and within the two groups (mTVM, TVM group) at six endpoints (before intervention and during follow-up clinical appointments 1–5 following intervention). Mixed design ANOVA will be carried out to determine the effects of the modified operation on subjective cure rate for POP and SUI, and the Bonferroni post hoc test will be used to test the difference between means. All statistical analyses will be completed after the final measurement of the last patient during the last clinical appointment after intervention. The repeated measure design with seven points in time allows us to monitor how patients change over time in both short-term (before/during intervention) and long-term situations (before/after intervention).

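### The questionnaire ANOVA uses the pre-surgery score as an outcome occasion instead of adjusting for it; its group-by-time term does test the hypothesis, but usually with less power than a pre-named, baseline-adjusted arm contrast

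*Protocol article*

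**What the plan says.** The Hypothesis section, under the primary outcome, expects that the mTVM group "will have a statistically higher improvement of continence measured by gynecological and urodynamic examination, and from the questionnaire administered before and after the intervention phase". That is a comparison of improvement between arms, and it includes the questionnaire.

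The Statistical analyses section ranks the PISQ-12 and PFDI scores as tertiary and gives two sentences on repeated measures:

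- A univariate repeated-measures ANOVA "will be used to determine the secondary outcome between and within the two groups", "at six endpoints (before intervention and during follow-up clinical appointments 1–5 following intervention".
- For the subjective outcomes: "Mixed design ANOVA will be carried out to determine the effects of the modified operation on subjective cure rate for POP and SUI", after which "the Bonferroni post hoc test will be used to test the difference between means".

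The second sentence lists no occasions. Later in the same section the design is said to have seven time points ("The repeated measure design with seven points in time allows us to monitor how patients change over time"). Table 1, in the row "Questionnaires: PISQ-12 and PFDI", schedules the questionnaires once before surgery and at 6 weeks, 6 months, 1, 2 and 3 years, and not at surgery itself. For the questionnaires the occasions are therefore six, and the first is the pre-surgery score. The section mentions no adjustment for that score.

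**The concern.** In a randomised comparison the pre-surgery score cannot carry an effect of the operation. Its value is as a predictor of later scores. Made an outcome level in a mixed design ANOVA, it leaves three standard terms, none of which is a focused estimate of how much more women improve with mTVM:

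- **Time** asks whether scores change after surgery, arms pooled. Both arms have surgery, so it is no comparison of the operations.
- **Group** asks whether the arms differ on average over all six occasions, one of which randomisation makes equal in expectation.
- **Group-by-time** asks whether the two profiles are parallel. This is the term that matches the hypothesis, but it spreads its power over every possible departure from parallel.

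At stake is a real, lasting questionnaire benefit that could be missed although the scores needed to detect it better are already collected. A significant result would also come without a single arm difference and confidence interval to report.

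**Working it through.** **Inputs.** From the article: 65 women per arm (Abstract, Methods), 1:1 allocation, two-sided 0.05, one pre-surgery and five follow-up scores (Table 1). The article gives no effect size, SD, correlation or power for the questionnaires, so there is no stated figure to reproduce; its sample size concerns the SUI cure rate only. Assumed here: unit-SD scores, equal correlation ρ of 0.3, 0.5 or 0.7 between occasions, no arm difference before surgery, and an arm difference d after it.

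**Sustained effect, d = 0.3 at all five follow-up visits, n = 65 per arm.** Power comes from the noncentral F distribution with noncentrality λ.

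1. *Group term.* The effect averaged over six occasions is 5d/6 = 0.25. λ = (n/2)(5d/6)² / [(1+5ρ)/6], on 1 and 128 df. At ρ = 0.5: 32.5 × 0.0625 / 0.5833 = 3.48.
2. *Group-by-time term.* The squared deviations of the arm difference from its mean sum to 0.25² + 5 × 0.05² = 0.075. λ = (n/2)(0.075)/(1−ρ), on 5 and 640 df. At ρ = 0.5: 32.5 × 0.075 / 0.5 = 4.88.
3. *Mean follow-up score adjusted for baseline.* λ = (n/2)d² / [(1+4ρ)/5 − ρ²], on 1 and 127 df. At ρ = 0.5: 32.5 × 0.09 / 0.35 = 8.36.

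| ρ | Group: λ, power | Group-by-time: λ, power | Baseline-adjusted mean: λ, power |
|---|---|---|---|
| 0.3 | 4.88, 59% | 3.48, 25% | 8.36, 82% |
| 0.5 | 3.48, 46% | 4.88, 35% | 8.36, 82% |
| 0.7 | 2.71, 37% | 8.13, 57% | 10.83, 90% |

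With the 81 per arm of the Sample size calculation section, the same formulas give 69/54/45%, 31/44/68% and 89/89/96%.

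**Unequal correlations.** A simulation of the same 0.3 SD effect over nine correlation patterns, equal and unequal, gave 34–61% for the group term, 23–56% for the Greenhouse–Geisser-corrected interaction and 49–90% for the adjusted comparison. The adjusted comparison led by 7–54 points over the group term and 17–58 points over the interaction.

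**Time term.** In 3,000 simulated trials with 65 per arm, an assumed 1 SD improvement in both arms and no arm difference, the time test rejected in every trial.

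**Does the interaction test the hypothesis?** In the same simulation at equal correlation 0.5, it rejected in 3.8–4.6% of trials with no arm difference, in 58% with a 0.4 SD difference and in 81% with 0.5 SD. It keeps its size and responds to differential improvement.

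**Other effect shapes, n = 65 per arm, ρ = 0.3/0.5/0.7.** For a baseline-adjusted contrast at one visit, λ = (n/2)d²/(1−ρ²) on 1 and 127 df.

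| Effect | Group-by-time | Adjusted, averaged over visits | Adjusted, at 3 years |
|---|---|---|---|
| 0.3 SD, sustained | 25/35/57% | 82/82/90% | 43/50/66% |
| Growing evenly to 0.6 SD at 3 years | 75/90/99% | 93/93/97.5% | 94.5/97.5/99.7% |
| 0.5 SD at 3 years only | 66/82/97% | 16/16/19% | 84/90/98% |

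The averaged contrast fails for a late-only effect. A contrast at 3 years does well there, but gives up much of the gain if the effect is sustained.

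**The case against.** The strongest reply is that the planned analysis is valid. A reader might infer that no standard term of this ANOVA addresses the hypothesis. That is not so: the null of the group-by-time term is equal change in both arms, and having the pre-surgery score among the occasions is what makes it a test of improvement. Lower power is a different matter from testing the wrong thing.

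Three further readings go beyond the text:

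- *That the time effect will be reported as an effect of the modification.* The article never says this. It plans comparisons between as well as within groups and directs the mixed ANOVA at the modified operation.
- *That the Bonferroni tests can only compare occasions.* The article does not say which means are compared. Arm comparisons at each visit are also a family that could be corrected.
- *That baseline adjustment always wins.* The last table shows that it does not.

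It is also fair to say that the six-occasion wording belongs to the sentence on the secondary outcome, so applying it to the questionnaires rests on Table 1. Naming the decisive term, the post hoc contrasts or a sphericity correction is commonly left to an analysis plan, so their absence from a journal article is no fault in itself. The trial was sized on the SUI cure rate and promises no power for the questionnaires.

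All of this stands. What it leaves untouched is that the article does choose a method, and for a lasting benefit that method makes poorer use of the baseline score than a readily available alternative.

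**Conclusion.** The point holds as an efficiency and reporting improvement, not as an error that invalidates the analysis. For an assumed sustained effect of 0.3 SD, with 65 per arm and equal correlation of 0.3 to 0.7, the two ANOVA terms that involve the arms have 25–59% power, against 82–90% for the baseline-adjusted mean. The reading that baseline is an outcome occasion is an inference from Table 1 and the neighbouring sentence, though a natural one. The size depends on assumed effects and correlations, and on the benefit being present through most of follow-up; for a benefit at 3 years only, the interaction beats the averaged contrast. Priority is low because the Statistical analyses section calls the questionnaires tertiary. It is not nil, because the Hypothesis section includes the questionnaire in the primary-outcome hypothesis.

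**What to change.** In the Statistical analyses section, replace the mixed design ANOVA of PISQ-12 and PFDI by a repeated-measures mixed model of the five post-surgery scores, with arm, visit, arm-by-visit and the pre-surgery score as covariate. Name one arm contrast in advance as the test, either averaged over visits or at one stated visit, and report it with its 95% confidence interval. State that within-arm change over time, and any Bonferroni comparisons of occasions, are descriptive.

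The cost is wording: Table 1 already schedules every score, and the model can be fitted in the planned software. Because such a model uses whichever follow-up scores are present, the text should also say whether last observation carried forward still applies to the questionnaires. The real price is commitment. The contrast has to be fixed before the data are seen, the averaged one loses power if the benefit appears only late, and a single-visit one loses power if it is sustained.

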## Discussion

Coexisting POP and SUI are increasingly recognized as a major health and financial concern affecting 63–80% of postmenopausal women [31]. TVM is the standard surgical method for the anatomical restoration of middle compartment Stage II–III prolapse; however, it should be supplemented with a mid-urethral sling to achieve better SUI treatment. Moreover, the combined mesh and sling operations yield unfavorably more frequent complication rates and may provoke voiding dysfunction and recurrent UTI. Furthermore, following the original TVM, some residual SUI can develop because of the backward dislocation of the mesh.

To the best of our knowledge, the present study is the first to investigate a surgical modification to TVM for more effective anti-incontinence. Should this newly developed modification be proved successful in treating SUI, it could be introduced in clinical practice due to its simplicity.

## Abbreviations

ANOVA: Analysis of variance
LOCF: Last observation carried forward
mTVM: Modified transvaginal mesh operation
PFDI: Pelvic Floor Distress Inventory
PFMT: Pelvic floor training
PISQ-12: Pelvic Organ Prolapse/Urinary Incontinence Sexual Questionnaire
POP: Pelvic organ prolapse
POP-Q: Pelvic organ prolapse quantification system
SUI: Stress urinary incontinence
TVM: Transvaginal mesh operation
UTI: Urinary tract infection
